### Design

This is a multi-center, patient-assessor-blinded, randomized, and controlled trial designed to evaluate the efficacy and safety of EA treatment in patients with mild to moderate first-episode depression and to compare the therapeutic effect between EA and ESC.

We will conduct this study at 4 centers, including Shanghai Municipal Hospital of Traditional Chinese Medicine, Shanghai Mental Health Center, Shanghai Pudong New District Nanhui Mental Health Center, and Shanghai Xuhui District Central Hospital. A total of 204 patients who meet the inclusion criteria will be recruited and randomly assigned into either group, receiving EA treatment with placebo drugs or ESC with sham acupuncture (SA) treatment. After a one-week baseline evaluation, participants will enter a nine-month observation period in this trial. Participants will receive the EA or SA treatment three times a week (every other day) for the first 8 weeks and twice a week (every two days) for the final 4 weeks. Participants will be assessed at the following time points: baseline (1 week before treatment), the 1st month of treatment (4 weeks after treatment starts), the 2nd month of treatment (8 weeks after treatment starts), the end of treatment (12 weeks after treatment starts), and follow-up (1 month, 3 months, and 6 months after treatment ends). All participants will complete the self-rated scales to assess their mental state and quality of life (see the detailed trial process in **Figures 1**, **2**). Throughout the trial, we will adhere to the Standards for Reporting Interventions in Clinical Trials of Acupuncture (STRICTA).

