### Randomization and blinding

This study uses a single-blind design, concealing group allocations from participants. Only acupuncturists will be aware of the assignments, but they will not be involved in any other part of the trial, including enrollment, evaluation, and data analysis. To increase blind validity, treatment will be performed in a separate room. Meanwhile, communication about the treatment or efficacy between acupuncturists and participants will be avoided to the maximum extent. At the conclusion of the 12-week intervention, the Bang blinding index will confirm the effectiveness of the blinding technique (12). The placebo drugs supplied by Shanghai Xinyi Huanghe Pharmaceutical Co. Ltd. have an identical appearance to the proprietary form of ESC (Bailote), which is supplied by Sichuan Kelun Pharmaceutical Co. Ltd. All medications are regularly dispensed once a week, with seven tablets per box. Patients can pick up their medication from the dispenser at their own corresponding number on the pre-packaged envelopes. Before the start of the trial, each investigator will receive multiple training sessions on the implementation of the standards of this study and will strictly adhere to the principle of separation of departments.

The study will use a block randomization method with a block size of four, facilitated by SPSS version 24.0 software. Eligible participants will be randomly assigned to either the EA or ESC group in equal proportions. An independent researcher will enclose the treatment allocation codes in sequentially numbered opaque envelopes, and another independent researcher will assign participants to the groups based on the corresponding number on the pre-packaged envelopes and randomization schedule. To confirm the effectiveness of the blinding, the acupuncturist will inquire with all participants whether they received EA or SA treatment at the end of the trial. All participants’ information will remain confidential to the acupuncturist and assessors throughout the trial.

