### Outcome measurement

#### Primary outcome

The primary outcome will be the mean change in HAMD-17 score from baseline to week 12. The HAMD-17 is a questionnaire designed to evaluate the symptoms of individuals diagnosed with depression, which is an observer-rated questionnaire consisting of 17 items (15). The scale uses either a 3-point or 5-point rating system and has demonstrated strong reliability and validity, making it a widely used tool in both research and clinical settings. A higher overall score indicates a higher level of depression, with scores ranging from 0 to 54; scores of 0–6 indicate a normal person without depression; 7–16, likely or suspected to have depression; 17–24, mild to moderate depression; ≥25, severe depression. This outcome data will be collected at baseline, during the treatment phase (at 4, 8, and 12 weeks), and at the 16-, 24-, and 36-week follow-ups.

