### Statistical analysis

Analyses will be conducted on the intention-to-treat (ITT) population, which comprises all qualified participants who meet the inclusion criteria, have received the intervention at least once, and have provided at least one outcome assessment. In statistical analysis, any missing primary outcome data will be replaced by the last observed data point, in accordance with the ITT principle. Additionally, a Per-Protocol Set (PPS) analysis will be employed to assess those participants who completed the trial without significant protocol violations. Data analysis for this study will be performed using the statistical software SPSS V.24.0. Descriptive statistical analysis will be used for all demographic and clinical characteristics of subjects, such as sex, age, and weight. We will validate the homogeneity of demographic characteristics and examine the variables between the two groups. The number of patients who change their medication dosage will also be counted, and the variations between the two groups and within each group will be analyzed. If measurement data follows a normal distribution and has homogeneity of variance, the data values will be reported as mean ± standard deviation (MD ± SD). Covariance analysis will be used to compare the data across different groups. If the data does not adhere to the assumed normal distribution, the median values (P25, P75) will be used to characterize it. The Mann-Whitney U nonparametric test will be used to compare between groups. The mean ± standard deviation will be used for the description of the continuous variables. Qualitative data will be expressed in terms of frequency and percentage. The student’s t-test will be utilized for comparing measurement data between two groups from baseline to the 6-month follow-up, while the rank sum test will be used for ranked data, and the χ2 test will be used for analyzing categorical data. A paired t-test was used for comparisons before and after treatment within a group, and an analysis of variance was used for comparisons among different groups. Repeated-measurement analysis of variance was used to compare groups at multiple observation points. A significance level of 2.5% will be used for all statistical analyses, using two-tailed testing. Subgroup analysis will be conducted to examine differences between different genders and across various age brackets.

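### Centre is not mentioned in any planned comparison although four hospitals of different types recruit; including it would give a small, cheap gain in precision, not the repair of a bias

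*Protocol article*

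**What the plan says.** The Design section states "We will conduct this study at 4 centers" and lists a traditional Chinese medicine hospital, two mental health centres and a district central hospital. The Primary outcome section states "The primary outcome will be the mean change in HAMD-17 score from baseline to week 12" and describes the HAMD-17 as a scale "which is an observer-rated questionnaire consisting of 17 items".

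On allocation, Randomization and blinding says "The study will use a block randomization method with a block size of four" and "Eligible participants will be randomly assigned to either the EA or ESC group in equal proportions". It does not say whether there is one list or one list per centre.

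The Statistical analysis section names these between-group methods:

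- covariance analysis: "Covariance analysis will be used to compare the data across different groups";
- for non-normal data: "The Mann-Whitney U nonparametric test will be used to compare between groups";
- Student's "t-test will be utilized for comparing measurement data between two groups from baseline to the 6-month follow-up";
- a rank sum test for ranked data, a chi-square test for categorical data, analysis of variance, and repeated-measures analysis of variance.

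Centre appears with none of them. The planned subgroups are gender and age only. The Abstract tells the reader that the article itself sets out the analysis plan for the primary and secondary outcomes in full.

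**The concern.** Hospitals of different types can be expected to differ in case mix and in how observers score the HAMD-17. An analysis that pools them leaves those differences in the error term. Where the arms happen to be unevenly spread over centres, some of the difference between centres also passes into the EA-ESC difference in that one trial. The trial judges this difference against a margin of -4 points, so avoidable noise makes it harder to show non-inferiority if it is true. A centre term deals with both situations, and every patient's centre is already known.

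**Working it through.** **Inputs.** From Sample size calculation: SD 11.5, margin -4, one-sided alpha 0.025 (the formula uses Z at 1 minus alpha), power 80%, 81 per arm, 102 per arm after 20% dropout. From Design: four centres. The share of variance due to centre, ρ, is not given anywhere. It is assumed here to be 0.02 to 0.10.

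**1. The plan's own figure.** n per arm = 2 × [σ(z₀.₉₇₅ + z₀.₈₀)/d]². With d = 4 + 1.1 = 5.1 this is 2 × [11.5 × 2.8016/5.1]² = 79.8, so 80 (plan: 81). Then 81/0.80 = 101.25, so 102 per arm and 204 in total. The match needs the 1.1-point difference taken in EA's favour. With the direction the text states (d = 4 - 1.1 = 2.9) the formula gives 247 per arm. That is a separate matter, so both distances are carried below.

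**2. What each named method can hold.** The t-test, Mann-Whitney test and plain chi-square test compare two samples and have no place for centre. Covariance analysis, analysis of variance and repeated-measures analysis of variance can each take centre as a factor, but the text names none.

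**3. Arms balanced within centre (separate lists).** The pooled SE is too large by 1/√(1-ρ) - 1. The true one-sided error is 1 - Φ(1.96/√(1-ρ)). Adjustment is worth 1/(1-ρ) - 1 more patients. The residual SD is 11.5√(1-ρ).

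| ρ | SE overstated | one-sided error | worth in patients | residual SD | power at 81 per arm, d = 5.1 | power at 81 per arm, d = 2.9 |
|---|---|---|---|---|---|---|
| 0 | 0 | 0.025 | 0 | 11.50 | 80.6% | 36.1% |
| 0.02 | 1.0% | 0.024 | 2% | 11.38 | 81.4% | 36.7% |
| 0.05 | 2.6% | 0.022 | 5% | 11.21 | 82.5% | 37.7% |
| 0.10 | 5.4% | 0.019 | 11% | 10.91 | 84.5% | 39.4% |

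The error falls below 0.025, so the pooled test is conservative.

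**4. One list across centres.** The shift from chance imbalance has mean zero and SD √(2V/102), where V is the variance of the centre means. Take centre means of -2, -0.7, 0.7 and 2 in equal centres:

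- V = (4 + 0.49 + 0.49 + 4)/4 = 2.245, which is 2.245/11.5² = 1.7% of the variance.
- SD of the shift = √(2 × 2.245/102) = 0.21 points, with a 95th percentile of about 0.4 in absolute value.
- SE of the EA-ESC difference = 11.5 × √(2/102) = 1.61 points.

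The check over the assumed range used 40,000 simulated trials per setting: 204 patients, blocks of four without regard to centre, centre means drawn at random with share ρ, and centre shares either equal or 40/30/20/10. The mean shift was within 0.003 of zero. Its SD ran from 0.19 to 0.45 points, and 95% of shifts lay within 0.40 to 0.92 points. The unadjusted test at a nominal two-sided 5% rejected in 4.9% to 5.1% of trials. With equal centres the empirical SE without and with centre was 1.597 and 1.596 (ρ = 0.02), 1.602 and 1.584 (ρ = 0.05), and 1.591 and 1.539 (ρ = 0.10). The gain is therefore between almost nothing and about 3% (1.591/1.539 = 1.034).

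**The case against.** The strongest reply is that this is an omission and not a wrong statement. The covariance sentence lists no covariates at all, not even the baseline score, and articles commonly leave such detail to the analysis plan. A reader might infer that the sentence excludes centre, or that none of the named methods could hold it. Neither is supported: the sentence is silent, and covariance analysis and both forms of analysis of variance accept a centre factor. That part of the reply stands.

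The reply does not remove the point, for two reasons. The Abstract says that the article gives the analysis in full. And the t-test, Mann-Whitney test and chi-square test are prescribed by name, so a later plan that used centre would have to replace them and not merely add detail.

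Three further objections stand as limits on its weight:

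- Nothing in the article shows that ratings or background care differ between centres. Entry is confined to HAMD-17 scores of 17 to 24 in patients who have never taken antidepressants, and investigators are trained repeatedly.
- The SD of 11.5 may already contain variation between centres, in which case adjustment is a gain over the planned power and not the filling of a shortfall.
- The two consequences are alternatives. Which one applies depends on how the list is built, and the article does not say.

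It is also fair to say that the section's larger weakness is that it fixes no single primary test. The fix below settles that too.

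**Conclusion.** The point holds as a modest matter of precision. Centre is not mentioned in any comparison, and three of the prescribed tests pool four unlike hospitals. With arms balanced within centres, the SE is overstated by 1.0% to 5.4% and the test is slightly conservative. With one list, the EA-ESC difference carries extra noise of about 0.2 points SD when centre means lie within ±2, and 0.19 to 0.45 over the whole assumed range. All of these figures rest on an assumed centre share, since the article gives none.

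A reader might infer that leaving centre out biases the EA-ESC difference or raises the risk of a false claim of non-inferiority. The article does not support that. Allocation is random and 1:1, so the shift averages zero, the unadjusted SE already covers it, and the type I error stays at or below its nominal level. Nor should a 95th-percentile shift of 0.4 points be read as a tenth of the 4-point margin lost: it is a chance deviation in either direction, small beside an SE of 1.61.

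**What to change.** In the Statistical analysis section, make the primary comparison a covariance model for week-12 change in HAMD-17 with treatment, baseline HAMD-17 and centre (a fixed factor with four levels). Read the EA-ESC difference and its confidence interval from that model, and compare the interval with the -4 margin. For PHQ-9 and SF-36 use the same model with the corresponding baseline score and centre. Compare the recovery rate with a Cochran-Mantel-Haenszel analysis stratified by centre.

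The cost is a change of wording and three degrees of freedom for centre out of about 200. No new data are needed. A centre that recruits very few patients may have to be pooled with another, so the rule for that should be written down before unblinding. Settling this in advance also removes any later choice about whether to adjust for centre.

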## Methods and analysis

### Hypothesis

We aim to provide definitive proof to validate the hypothesis that EA is not inferior to escitalopram (ESC) in the treatment of mild to moderate first-episode depression.

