### Sample size calculation

The non-inferiority hypothesis is based on the results of a previous study (11). HAMD-17, as the primary outcome, decreased by 11.3 points in the premedication group and by 10.2 points in the EA group, with an equal standard deviation of 11.5 points. Following these parameters, the proposed non-inferiority boundary is set at -4 points, with a level one type I statistical error equivalent to 0.025 and a desired statistical power standing at 80%. These calculations are supported by the analytical tools implemented in PASS 15.0. The results were obtained for a required sample size of 81 cases per group, and considering a 20% drop rate, 102 cases need to be included in each group, totaling 204 cases. The formula employed to determine the sample size in this trial was listed as:

$${\text{n}}_{\text{A}}={\text{k}}_{{\text{n}}_{\text{B}}}\;\text{and}\;{\text{n}}_{\text{B}}=\left(1+\frac{1}{\text{k}}\right){\left(\sigma \frac{Z_{1-\alpha }+Z_{1-\beta }}{\mu_{A}-\mu_{B}-\delta }\right)}^{2}$$

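### No single analysis is fixed for the primary HAMD-17 comparison, and the Mann-Whitney branch does not address a margin of 4 mean points

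*Protocol article*

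**What the plan says.** The Hypothesis section sets out to show that EA is not inferior to escitalopram. The Primary outcome section fixes the quantity: "The primary outcome will be the mean change in HAMD-17 score from baseline to week 12". The Sample size calculation section fixes the margin on that scale: "the proposed non-inferiority boundary is set at -4 points".

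The Statistical analysis section mentions neither the margin nor a confidence interval, and assigns no test to the primary outcome. Its rules cover all measurement data, so they reach HAMD-17 by default:

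- Normal with homogeneous variance: mean and SD are reported, and "Covariance analysis will be used to compare the data across different groups".
- Not normal: median and quartiles are reported, and "The Mann-Whitney U nonparametric test will be used to compare between groups".
- No distributional condition: Student's t-test between groups from baseline to the 6-month follow-up.
- No distributional condition: analysis of variance among groups.
- No distributional condition: "Repeated-measurement analysis of variance was used to compare groups at multiple observation points".

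The section also sets a 2.5% two-tailed level for every analysis. The Abstract says that full details of the analysis plan for the primary and secondary outcomes are given in this article.

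**The concern.** Five between-group procedures can be applied to one continuous endpoint. A distributional check on the outcome data switches between two of them, and the other three overlap with no rule of precedence. If they disagree, the document does not say which one answers the trial's question.

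The switch also changes the question. ANCOVA estimates a difference in means, on the scale of the margin. Mann-Whitney asks whether values in one arm tend to exceed those in the other; as written, its null is no difference. Failing to reject that null does not show that EA is less than 4 points worse. If the primary endpoint went down this branch, the trial could end with a p-value that says nothing about its own hypothesis.

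**Working it through.** **Inputs.** From the Sample size calculation section: "decreased by 11.3 points in the premedication group and by 10.2 points in the EA group", "with an equal standard deviation of 11.5 points", margin 4 points, type I error 0.025 (used one-sided in the printed formula), power 80%, 81 per group before dropout. From the Statistical analysis section: 2.5%, two-tailed.

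**The plan's own figure.** For equal groups, n = 2 × (SD × (1.960 + 0.842) / distance)².

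- EA 1.1 points worse, as stated (distance 4 - 1.1 = 2.9): n = 246.9, so 247.
- No true difference (distance 4): n = 129.8, so 130.
- EA 1.1 points better (distance 5.1): n = 79.8, so 80, or 81 with the t distribution.

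So 81 appears only with the sign of the 1.1-point difference reversed. That is a separate matter; 81 is used below only as the plan's evaluable number per arm. The dropout step, 81 / 0.8 = 101.25, so 102, reproduces.

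**Mann-Whitney as written, with EA exactly at the margin.**

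- Standard error of a mean difference: 11.5 × √(2/81) = 1.807.
- Standardised deficit: 4 / 1.807 = 2.214.
- For normal data the rank test keeps a fraction √(3/π) = 0.977 of this: 2.163.
- Two-tailed 2.5% critical value: 2.241.
- Probability of non-significance: Φ(2.241 - 2.163) = Φ(0.078) = 0.53.

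A simulation (10,000 trials, normal data) gives 54%. At 102 per arm (no dropout), the standard error is 11.5 × √(2/102) = 1.610 and the standardised deficit for the rank test is 0.977 × 4 / 1.610 = 2.427. The probability is then Φ(2.241 - 2.427) = 0.43. A procedure that misses a deficit of the full margin about half the time cannot support non-inferiority through a non-significant result.

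**A margin-shifted Mann-Whitney, which the plan does not specify.** Add 4 points to each improvement in the EA arm and test one-sided at 2.5%. The true mean difference is exactly -4, so every declaration of non-inferiority is an error (81 per arm, 10,000 trials):

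| Shape of improvement scores | Shifted Mann-Whitney | Welch t |
|---|---|---|
| Both arms normal, equal SD (pure shift) | 2.6% | 2.7% |
| EA arm left-skewed, control normal | 13.5% | 3.2% |
| EA arm right-skewed, control normal | 0.1% | 1.8% |

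The skewed shapes are assumed (exponential, SD 11.5, EA arm only) and deliberately strong. The shifted rank test holds its level for the mean margin when the arms differ by location alone, and can be far off in either direction otherwise. The mean-based test stays near 2.5% even with this skew.

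**Confidence level.** A one-sided error of 0.025 corresponds to a two-sided 95% interval; 2.5% two-tailed corresponds to 97.5%. At 81 per arm and SD 11.5 (unadjusted, normal approximation), the half-widths are 1.960 × 1.807 = 3.54 and 2.241 × 1.807 = 4.05. With the wider interval, an observed difference of zero would fail the 4-point margin; with the narrower one it would pass. The primary analysis therefore has to state its level.

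**The case against.** The strongest reply is that the section is a general catalogue for all continuous variables, including PHQ-9 and SF-36, and that some entries plausibly serve different purposes, such as repeated-measures ANOVA for the course over time. A separate analysis plan could name the primary test. The first part is fair: choosing the favourable test is a risk that the text leaves open, not a stated intention. The second part carries little weight here, because the article promises the full analysis details itself and prescribes competing procedures. The defect lies in what is written.

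It is also fair that Mann-Whitney is not alone. ANCOVA and the t-test are listed without the margin too. They could yield a confidence interval for a mean difference; the Mann-Whitney test does not. Under a pure location shift, a shifted rank test or a Hodges-Lehmann interval would serve, but neither is specified.

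Some stronger readings are tempting but unsupported:

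- *Normality selects among all the listed tests.* It governs only ANCOVA against Mann-Whitney; the others carry no such condition.
- *The check is made on unblinded data.* The section does not say so. The choice is data-dependent, no more.
- *Repeated-measures ANOVA would drop anyone with a missed visit.* The section fills missing primary outcome data with the last observed value, so this does not follow for HAMD-17.
- *Week-12 scores will pile up near zero and force the rank test.* Entry scores of 17 to 24 less the assumed falls of 10.2 to 11.3 suggest a mean around 9 to 10. Skew is possible, but it is not documented.
- *An unadjusted test wastes a large share of the variance.* The endpoint is change from baseline, which already subtracts baseline. The documents give no correlation from which to size any further gain.

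**Conclusion.** The point stands. The article fixes no single primary analysis for the week-12 HAMD-17 change, lets a distributional check move it between a comparison of means and a comparison of ranks, and ties none of its five between-group procedures to the -4 point margin. Followed as written, the non-normal branch gives a test of no difference that would be non-significant in about 54% of trials with EA truly 4 points worse. That figure assumes 81 per arm, SD 11.5, normal data and the 2.5% two-tailed level; with 102 per arm it is about 43%. The error rates for the shifted test depend on the assumed skewed shapes and show a direction of risk, not a forecast. How likely the Mann-Whitney branch is to be reached cannot be judged from the documents. This should be corrected before the data are analysed.

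**What to change.** Name one primary analysis that applies whatever the normality check shows: the ANCOVA already listed, with baseline HAMD-17 as covariate, giving the adjusted mean difference in HAMD-17 change at week 12. State the direction of subtraction (improvement on EA minus improvement on escitalopram), and declare non-inferiority if the lower bound of the two-sided 95% confidence interval lies above -4. That level matches the 0.025 one-sided error of the sample size section; reconcile the two-tailed 2.5% in the Statistical analysis section with it. If residuals are skewed or variances unequal, use heteroscedasticity-robust standard errors and keep the same estimate. Label Mann-Whitney, the t-test, ANOVA, repeated-measures ANOVA and the other time points as supportive.

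The cost is wording in the analysis section. No data collection, visit or sample size changes because of this point.

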**Methods and analysis:**

This is a multi-site, single-blind, randomized controlled trial with two parallel arms. A total of 204 eligible patients will be randomly allocated to two groups: the EA group (receiving EA treatment with placebo drugs) and the ESC group (receiving escitalopram and sham acupuncture treatment). Treatment will last 12 weeks, with 3 sessions per week for the first 8 weeks, decreasing to 2 per week for the remaining 4 weeks. The primary outcome will be the score of the 17-item Hamilton Depression Rating Scale (HAMD-17), and the secondary outcomes will include depression recovery rate, depression remission rate, Patient Health Questionnaire-9 (PHQ-9), 36-Item Short Form Survey Instrument (SF-36), and the dose and frequency of ESC. The Treatment Emergent Symptom Scale (TESS) will be used to assess all adverse effects. Full details of the statistical analysis plan for the primary and secondary outcomes will be described in this article.

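### The hypothesis and sample size are non-inferiority with a -4 point margin, but the Statistical analysis section plans only tests of difference and states no comparison with the margin

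*Protocol article*

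**What the plan says.** The Hypothesis section sets out to show that "EA is not inferior to escitalopram (ESC) in the treatment of mild to moderate first-episode depression". The Primary outcome section fixes the endpoint: "The primary outcome will be the mean change in HAMD-17 score from baseline to week 12". The Sample size calculation section states that "the proposed non-inferiority boundary is set at -4 points". It takes α as 0.025 and power as 80%. The printed formula uses Z at 1-α, so the 0.025 is one-sided.

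The Statistical analysis section then names covariance analysis, the Mann-Whitney U test if data are not normal, Student's t-test ("t-test will be utilized for comparing measurement data between two groups from baseline to the 6-month follow-up"), rank sum, chi-square and paired t-tests, analysis of variance and repeated-measures analysis of variance. It assigns none of these specifically to the primary outcome. It ends its testing rules with "A significance level of 2.5% will be used for all statistical analyses, using two-tailed testing". It defines an ITT set and adds a per-protocol analysis. It does not mention non-inferiority, the -4 margin or a confidence interval. The margin appears only in the sample size section.

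On how complete this is meant to be, the abstract says "Full details of the statistical analysis plan for the primary and secondary outcomes will be described in this article".

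**The concern.** Each between-group test listed has, as described, a null hypothesis of no difference. Rejecting that null shows that the arms differ, and failing to reject it shows nothing about the margin. A non-inferiority claim needs a different null (EA worse by 4 points or more), which in practice means setting a confidence limit against -4. No step in the analysis section does this.

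The trial's one confirmatory claim therefore has no rule attached to it. The rule would have to be chosen later, possibly after results are known. The most obvious misuse would be to treat a non-significant p-value as proof of non-inferiority, and noisier data would make that conclusion easier to reach. The two-tailed 2.5% sentence adds a direct conflict, because it does not match the one-sided 0.025 on which the trial was sized.

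**Working it through.** **Inputs.** From the Sample size calculation section: reductions of 11.3 points (the premedication group, taken here as the drug comparator) and 10.2 points (EA), SD 11.5 in both groups, margin -4, α 0.025, power 80%, 81 per group, 20% dropout, 102 per group. Allocation is 1:1. From the Statistical analysis section: two-tailed 2.5%.

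**1. Reproduce the plan's figure.** With k = 1, n = 2 × [σ(z₀.₉₇₅ + z₀.₈₀)/d]², where d is the distance from the assumed difference to the margin.
- d = 1.1 + 4 = 5.1: 2 × [11.5 × 2.802/5.1]² ≈ 79.8, so 80 per group (normal) or 81 (noncentral t). Then 81/0.80 = 101.25, so 102 per group and 204 in total. This matches.
- d = 4 - 1.1 = 2.9: 247 (normal) or 248 (t). This does not match.

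The sizing is therefore a one-sided 0.025 comparison with -4. It counts the 1.1-point difference in EA's favour although the text has EA doing worse. That is a separate matter. It is noted here only because the 80% power below depends on it.

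**2. What a margin comparison needs at 81 per arm.** SE = 11.5 × √(2/81) = 1.81.
- Two-sided 95% interval: half-width 1.975 × 1.807 = 3.57. The observed EA minus ESC difference in improvement must exceed -4 + 3.57 = -0.43.
- Two-sided 97.5% interval, as the two-tailed 2.5% sentence would imply: half-width 2.263 × 1.807 = 4.09. The observed difference must exceed -4 + 4.09 = +0.09.

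**3. What the listed test of difference does.** At two-tailed 2.5% and 81 per arm, any observed difference between -4.09 and +4.09 is non-significant. Observed differences from -4.09 to -0.43 would thus be non-significant and yet fail the 95% margin comparison.

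**4. Error rate if non-significance were read as non-inferiority.** Take EA truly 4 points worse, SD 11.5. The noncentrality is 4/1.807 = 2.21 at 81 per arm and 4/1.610 = 2.48 at 102, where 1.610 = 11.5 × √(2/102).

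| Analysed per arm | Non-significant, two-sided 2.5% | Non-significant, two-sided 5% |
|---|---|---|
| 81 | 51.8% | 40.5% |
| 102 | 41.0% | 30.4% |

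The designed error rate at the margin is 2.5%. As a sensitivity check with an SD of 8, which is an assumption and not in the article, the figures at 81 per arm are 18.0% and 11.5%.

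**5. Effect of the two-tailed 2.5% sentence on a proper margin test.** With d = 5.1, power at 81 per arm is 80.1% with a 95% interval and 71.2% with a 97.5% interval. Restoring 80% with the latter needs 98 per group, or 98/0.80 = 122.5, so 123 with dropout.

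**6. The non-normal fallback.** The Mann-Whitney test compares distributions and gives no mean difference. The margin and the primary outcome are both defined on mean change, so this route leaves nothing to compare with -4.

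**The case against.** The strongest defence is that everything needed for the test is in the article: the hypothesis, the endpoint and time point, the margin with its sign, and the error level. The ANCOVA or the t-test would give a mean difference whose interval could be set against -4. This stands, and it limits the point. A reader might infer that the trial is incapable of testing non-inferiority. The documents do not support that, because what is missing is a stated rule and not the data or a usable model. The exception is the Mann-Whitney route.

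A reader might also infer that the investigators will count a non-significant result as success, or that this is the only path to a positive claim. Neither is supported. The article does not say how the hypothesis will be decided, and a significant difference in EA's favour would also establish non-inferiority. The error rates in the table are therefore conditional on a reading that the article does not state.

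Nor can one infer that the per-protocol analysis has been demoted. The text introduces it as a further analysis without ranking it, and how the two sets combine may reasonably be left to a fuller plan.

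One could reply that the margin comparison belongs in a separate SAP. That does not succeed here. The abstract says the article gives the full plan for the primary outcome, and the analysis section does more than stay silent: it fixes two-tailed testing at 2.5% for all analyses, which contradicts the one-sided sizing.

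**Conclusion.** The point holds in this form: the stated analysis does not test the stated hypothesis. The hypothesis and sample size are non-inferiority against -4 at one-sided 0.025. The analysis section offers only tests of difference, at a level that does not match the sizing, and gives no decision rule.

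If non-significance were taken as non-inferiority, the false-conclusion rate with EA truly 4 points worse would be about 52% (81 per arm) or 41% (102 per arm), against 2.5%. This rests on the article's SD of 11.5, two-sided 2.5% testing and a t-test. It would be smaller with a smaller SD.

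If the margin comparison is made but the two-tailed 2.5% sentence is left in force, power at 81 per arm falls from 80% to about 71%, on the sizing's own implicit assumption that EA is better by 1.1 points.

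This should be corrected before any unblinded data are seen, because it governs the trial's only confirmatory claim.

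**What to change.** In the Statistical analysis section:

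- Name one primary analysis: ANCOVA of HAMD-17 change from baseline to week 12, adjusted for baseline HAMD-17, giving the EA minus ESC difference in mean improvement with its two-sided 95% confidence interval.
- State the rule: non-inferiority is declared only if the lower limit of that interval (one-sided 0.025) lies above -4 points.
- Exempt this analysis from the sentence setting two-tailed 2.5% for all analyses, so that the analysis matches the sizing.
- State that the Mann-Whitney test does not replace this analysis if the data look non-normal.
- Report the same interval-versus-margin comparison in the per-protocol set already planned.
- State that a non-significant difference is not evidence of non-inferiority.

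The cost is a change of wording, with no new data or visits and no change to the planned 204 patients. If the sponsor does intend two-tailed 2.5% for the primary comparison, the sample size would have to be revisited.
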